**Methods:**

The Mental Health Intervention With Digital Applications (MIND-APP) trial is a 3-arm randomized controlled trial (1:1:1 allocation) conducted fully remotely via a bespoke smartphone research platform. A total of 1000 Norwegian residents aged 16 years or older with mild to moderate symptoms of anxiety and/or depression will be recruited through national digital outreach. Coprimary outcomes are changes in anxiety (Generalized Anxiety Disorder-7) and depression (Patient Health Questionnaire-9) scores from baseline to postintervention (2-4 weeks). Secondary outcomes include health-related quality of life (EQ-5D-5L), quality-adjusted life years accrued over 6 months, functional impairment (Work and Social Adjustment Scale), health care resource use, and adverse events. Incremental cost-effectiveness ratios for Tankevirus and Grubl relative to placebo will be estimated from the perspective of public health services.

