#### Postintervention Follow-Up

Upon completion of the last program element or after 4 weeks, participants will be invited to respond to the postintervention follow-up. This comprises all clinical questionnaires (PHQ-9, GAD-7, EQ-5D-5L, and WSAS), retrospective health care resource use over the last 4 weeks, questions about co-occurring treatment, SUS, and the CSQ-8.

Participants who have not submitted any outcome assessment within 2 weeks of the scheduled assessment date, despite automated push notification reminders, will be considered lost to follow-up for that time point. This rule applies at postintervention and at 3- and 6-month follow-up.

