### Safety Considerations

Use of MIND-APP is considered safe for users. Tankevirus and Grubl provide videos with psychoeducational contents, and the placebo app will include a set of short attention/concentration games to be done in a few minutes each day. Identifiable information is stored separately from recorded trial data. However, we cannot conclusively exclude the possibility that study participants experience discomfort while using the apps.

While the intervention type involved in MIND-APP is unlikely to be associated with most types of adverse events, monitoring is conducted as per clinical RCT conventions.

Adverse events are defined as any untoward medical occurrence in a participant to whom a medicinal intervention has been administered, including occurrences that are not necessarily caused by or related to that product. Serious adverse events are defined as any untoward medical occurrence that: results in death, is life-threatening, requires inpatient hospitalization or prolongation of existing hospitalization, results in persistent or significant disability/incapacity, or consists of a congenital anomaly or birth defect. The term “life-threatening” in the definition of “serious” refers to an event in which the participant was at risk of death at the time of the event; it does not refer to an event that hypothetically might have caused death if it were more severe.

Other “important medical events” may also be considered a serious adverse event when, based on appropriate medical judgement, the event may jeopardize the participant and may require medical or surgical intervention to prevent one of the outcomes listed above.

Participants may report potential adverse events via a dedicated menu option in the app or by contacting the trial team directly by phone or email. Adverse events will be collected systematically from randomization through the 6-month follow-up assessment.

While unlikely for most users, repeated self-monitoring or exposure to sensitive psychoeducational topics might prompt distress, anxiety, sadness, or increased rumination in some participants.

Self-monitoring could lead to heightened symptom awareness, possibly resulting in perceived or actual increases in distress.

Frustration, confusion, or distress could result from app malfunctions, usability challenges, or notification fatigue.

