Worsened symptoms will be captured by the recording of symptoms in the trial. In addition, a menu item not present in the regular Tankevirus and Grubl apps will be provided, allowing users to report any discomfort and to optionally complete PHQ-9 and GAD-7 to report their current mental health. Users indicating severe depression (PHQ-9 score ≥20) or reporting score ≥2 on item 9 of PHQ-9, suggesting suicidal ideation, will be provided with information on where they can seek help (Multimedia Appendix 4).

The relationship of each adverse event to the intervention must be determined by a qualified individual according to the following definitions:

Unrelated: where an event is not considered to be related to the intervention.Possibly: although a relationship to the intervention cannot be completely ruled out, the nature of the event, the underlying disease, concomitant medication, or temporal relationship make other explanations possible.Probably: the temporal relationship and absence of a more likely explanation suggest the event could be related to the intervention.Definitely: the known effects of the intervention, its therapeutics class, or findings from challenge testing suggest that the intervention is the most likely cause.

All adverse events (serious adverse events) labeled possibly, probably, or definitely will be considered related to the intervention.

We do not anticipate that the study interventions (Tankevirus, Grubl, or the placebo app) should result in any adverse events but this section is included in case such events are reported so that they can be considered for causal links to the study. Only adverse events that are clinically judged by the research site monitoring board as being caused by the trial intervention will be reported in accordance with Akershus University Hospital guidelines. Participants will be asked at follow-up whether they have experienced any side effects or medical events while participating in the MIND-APP trial by way of a reporting option in the app. Participants may also report potential serious adverse events via phone or email correspondence with the trial team.

We do not anticipate any serious adverse events due to the digital interventions or data collection.

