#### Secondary Outcomes

Secondary outcomes WSAS and EQ-VAS will be compared between baseline and the 3 primary follow-up time points (4-week, 3-month, and 6-month) in the same manner as the primary outcome.

EQ-5D-5L will be used to determine differences in accrual of QALYs between the trial arms using Norwegian population preference weights. The primary QALY analysis will include only the observed period, with separate analyses using extrapolation to 1- and 3-year time horizons.

The score on the EQ-5D-5L anxiety and depression dimension will be analyzed as a separate measure in the same way as the primary outcome.

The proportion of participants reporting worsened symptoms and treatment-emergent adverse events will also be compared.

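### The rule on which adverse events are reported does not say what reporting covers, and it disagrees with the protocol's own relatedness scale, assessor and all-cause comparison

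*Protocol article*

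**What the plan says.** All references are to the protocol article.

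- **Reporting rule (Safety Considerations).** "Only adverse events that are clinically judged by the research site monitoring board as being caused by the trial intervention will be reported". The sentence then continues: "caused by the trial intervention will be reported in accordance with Akershus University Hospital guidelines".
- **Definition (same section).** An adverse event is any untoward medical occurrence, "including occurrences that are not necessarily caused by or related to that product".
- **Collection (same section).** "Adverse events will be collected systematically from randomization through the 6-month follow-up assessment". Participants are also to be asked about side effects and medical events at follow-up, through a reporting option in the app.
- **Relatedness (same section).** A qualified individual grades each event on a four-level scale, and events "labeled possibly, probably, or definitely will be considered related to the intervention".
- **Analysis (Statistical Analysis Plan, Secondary Outcomes).** "The proportion of participants reporting worsened symptoms and treatment-emergent adverse events will also be compared". No relatedness limit is stated.
- **Outcome status (Abstract, Methods).** The secondary outcomes there include "health care resource use, and adverse events". The list under Assessments, Secondary Outcomes, does not name adverse events.
- **Oversight (Ethical Considerations).** The Trial Oversight Committee doubles as the Data Safety Monitoring Board. No body with the title used in the reporting rule appears there.

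**The concern.** The reporting rule is the only sentence that says which adverse events will be reported. It opens with a restriction, and nothing in it expressly confines it to institutional notification. In a registered report, such sentences are likely to be applied as written.

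The stake is the between-arm safety comparison. The protocol itself names distress, anxiety, sadness and increased rumination as possible effects of the apps. In a single participant these cannot readily be told apart from the condition that brought the person into the trial, and the definition of *possibly* related cites the underlying disease as an alternative explanation. Such an event could easily fall short of being judged caused by the app. Randomisation makes that judgement unnecessary: a count of all events by arm shows an excess without anyone attributing individual cases. If only events judged causal reached the results, the comparison would rest on fewer events and on an unspecified judgement.

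**Working it through.** **Step 1: set the statements side by side.**

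| Statement | Which events count | Who judges |
|---|---|---|
| Definition and collection (Safety Considerations) | all, whatever the cause | no judgement |
| Comparison by arm (Statistical Analysis Plan, Secondary Outcomes) | treatment-emergent, no relatedness limit | no judgement |
| Relatedness scale (Safety Considerations) | *possibly*, *probably*, *definitely* count as related | a qualified individual |
| Reporting rule (Safety Considerations) | judged caused by the intervention | a monitoring board |

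**Step 2: test each reading of the reporting rule.**

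- *Reporting means trial results.* Row 4 contradicts rows 1 and 2: an unrestricted comparison cannot be published if only events judged causal are reported.
- *Reporting means notification under hospital guidelines.* Rows 1 and 2 are untouched. Rows 3 and 4 still disagree. Being possibly related is a lower bar than being judged caused, the assessor differs, and no reason is given for a second threshold or a second assessor.

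The conflict between rows 3 and 4 therefore holds on both readings. The conflict with rows 1 and 2 holds only on the first.

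**Step 3: what a filter would cost, if it governed the results.** The documents give no adverse event rate, so there is no plan figure to reproduce. The following is an illustration with assumed inputs.

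- n = 300 per arm, the number required per arm in Sample Size Calculation.
- Assumed event proportions p1 and p2 in two arms.
- Assumed share f of events that pass the filter, equal in both arms.
- Two-sided α = 0.05, normal approximation. With p̄ the mean of f·p1 and f·p2:
  - SE0 = √[2·p̄(1−p̄)/n]
  - SE1 = √{[f·p1(1−f·p1) + f·p2(1−f·p2)]/n}
  - power = Φ[(f·|p2−p1| − 1.96·SE0)/SE1]

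Worked case, 5% vs 10%, f = 1: p̄ = 0.075, SE0 = 0.0215, SE1 = 0.0214, power = Φ[(0.05 − 0.0422)/0.0214] ≈ 0.64.

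| Assumed rates | f = 1 | f = 0.50 | f = 0.25 | f = 0.10 |
|---|---|---|---|---|
| 5% vs 10% | 0.64 | 0.36 | 0.20 | 0.11 |
| 10% vs 18% | 0.81 | 0.48 | 0.27 | 0.13 |

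With 333 per arm (1000/3, no attrition), 5% vs 10% gives 0.69, 0.40, 0.22 and 0.11. The direction is the same throughout; the size depends wholly on the assumed rates and on f.

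**Step 4: what the filter would not touch.** Worsened symptoms are captured by PHQ-9 and GAD-7 at each scheduled assessment and compared by arm with no causality judgement. The loss in Step 3 therefore concerns other events: hospitalisation, other medical events, and the frustration or confusion from malfunctions that the protocol mentions. It also concerns distress that scores at three follow-ups miss, including in participants who do not respond.

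**Step 5: collection.** The postintervention contents are listed as "This comprises all clinical questionnaires (PHQ-9, GAD-7, EQ-5D-5L, and WSAS), retrospective health care resource use over the last 4 weeks", followed by co-occurring treatment, SUS and CSQ-8. The 3- and 6-month lists are shorter. Neither these lists nor Table 1 shows an adverse event item, although the safety section promises a follow-up question.

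**The case against.** The strongest reply is that the reporting rule must be read to its end. The reference to hospital guidelines makes institutional notification a natural meaning. The protocol then already has what is wanted: a cause-independent definition, collection to 6 months, weekly review of adverse events by the study team, and an unrestricted comparison by arm. No sentence says that the causality judgement filters that comparison. This stands, and it is why the conflict with the planned comparison is an ambiguity and not an established contradiction.

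A reader might go further and infer that the plan conceals a harm signal. The documents do not support that. The named harms of increased anxiety or sadness should largely show in the symptom scores, which are compared by arm without any filter.

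A reader might also infer that judgements will be biased by knowledge of the app, or will mostly come back as unrelated. Participants know their app, but allocation is to be blinded to researchers and statisticians, and the article does not say whether the board sees it. Neither inference is established.

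Nor can it be said that events are not solicited, since a follow-up question is promised. Its absence from Table 1 may be a matter of listing in a condensed article.

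What the reply does not remove is the mismatch of threshold and assessor within the safety section, the undefined board, and the missing statement of what reporting covers.

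**Conclusion.** The point holds as a defect of wording that should be settled before recruitment. Two things are certain from the text: the safety section uses two thresholds (possibly related, and caused) and two assessors (a qualified individual, and a board not named in the oversight structure), and it does not say what reporting covers. The conflict with the all-cause definition, the outcome listing and the between-arm comparison depends on the literal reading.

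The statistical cost is conditional in the same way. If the filter governed published results, power to see an imbalance could fall substantially under the assumed rates in the table above. Those rates are not the trial's, and the loss would not extend to symptom worsening measured by PHQ-9 and GAD-7. If the rule concerns institutional notification only, the planned comparison loses nothing.

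**What to change.** - State that all adverse and serious adverse events are tabulated and compared by randomised arm regardless of judged cause, with relatedness as an extra column on the existing scale (*possibly* or higher counts as related).
- Limit the causation sentence to notification under the hospital's guidelines.
- Name one assessor and one relatedness threshold, and either define the monitoring board or replace it with a body listed under Ethical Considerations.
- Make the promised follow-up question a fixed item at postintervention, 3 months and 6 months, and add a row for it to Table 1.

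The cost is a few sentences, one in-app item and one table row, with no data yet collected. The downside is a longer table of mostly unrelated events. The change is right under either reading of the present sentence.

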### Sample Size Calculation

Sample size calculation assumptions were based on self-reported data from the Tankevirus app in Norway combined with information from 2 meta-analyses of mobile apps for mental health [11,32]. The 2 meta-analyses both indicate high variability both in quality of evidence and estimated effect sizes. Assuming low to moderate effects, we assumed Cohen *d* of 0.3. For a single outcome, targeting 80% power and a critical α of .05, regular power analyses indicate a need for 176 participants in each study arm. However, the coprimary end points of the trial and expected correlation between the GAD-7 and the PHQ-9 imply reduced power.

To better reflect these factors, we built a Monte Carlo simulation based on recorded responses to the PHQ-4, which comprises 2 questions from the GAD-7 and 2 questions from the PHQ-9 collected from the existing Tankevirus app. We assume a correlation of approximately 0.7 between the PHQ-9 and the GAD-7. Assuming a distribution of responses taken from these self-report data, targeting 80% power, with a critical α=.05, the analyses suggested that 300 participants per arm are required for comparisons between each active arm and the placebo condition, given the coprimary end points and the observed proportions having problems with either anxiety or depression but not both.

The trial is powered for separate comparison of each app to placebo, but is not powered to allow meaningful comparison of the outcomes between Tankevirus and Grubl. The recruitment target is 1000 participants to account for attrition.

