### Statistical Analysis Plan

#### Statistical Methods

Observed values from the per-protocol population will be used for the primary analysis. Sensitivity analyses including complete cases and an intention-to-treat analysis with imputed values will also be conducted. The RCT app automatically records all use of all app functions with timestamps, and per-protocol compliance will be determined as having viewed the 3 primary videos of the Tankevirus and Grubl arms or having completed the 3 primary units of the placebo arm. Participants with compliance below the per-protocol threshold will be included in the intention-to-treat analysis but not the per-protocol analysis.

The primary analysis will use an analysis of covariance (ANCOVA) framework: the postintervention score will be the dependent variable, treatment arm the primary factor, and baseline score a covariate. This adjusts for regression to the mean and improves precision. Stratification variables used in randomization (sex, age group, and symptom severity) will also be included as covariates.

The trial compares 2 separate treatments with placebo, and the literature is divided on whether testing should be adjusted for multiplicity [33]. To account for the 2 treatment-vs-placebo comparisons while controlling the familywise type I error rate, Dunnett procedure will be applied to the ANCOVA-adjusted (least squares) means, exploiting the positive correlation between the 2 test statistics arising from the shared placebo arm [34].

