### Strengths and Limitations

Strengths include (1) registered report format with prespecified analyses, (2) large sample (n=1000) providing adequate power for primary comparisons, (3) fully remote design enabling broad population reach within Norway, (4) matched digital placebo controlling for nonspecific effects, (5) integration of clinical and economic outcomes, (6) coproduction with lived experience experts, and (7) comprehensive open science practices.

Limitations include (1) self-reported outcomes only; (2) digital recruitment may favor younger, more digitally literate participants; (3) the placebo, designed to minimize harm, may provide some therapeutic benefit, attenuating effect sizes; (4) Norwegian-only restriction limits generalizability; (5) not powered for direct Tankevirus vs Grubl comparison; and (6) 6-month follow-up does not capture long-term durability.

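### The stated 80% power is not supported for the planned Dunnett-adjusted test, and 1000 recruits leave exactly 10% for every loss from a per-protocol, observed-value analysis

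*Protocol article*

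**What the plan says.** The Sample Size Calculation section starts from the effect size: "Assuming low to moderate effects, we assumed Cohen *d* of 0.3". For one outcome at 80% power and a critical alpha of .05, "regular power analyses indicate a need for 176 participants in each study arm".

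A Monte Carlo simulation then follows. It assumes a GAD-7/PHQ-9 correlation of about 0.7, and its result is reported as "targeting 80% power, with a critical α=.05, the analyses suggested that 300 participants per arm are required". The factors named as reflected are the coprimary end points, their correlation, and the share of participants with only one of the two problems. The section adds: "The recruitment target is 1000 participants to account for attrition". It gives no attrition rate.

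The Statistical Methods section fixes the test. To control the familywise error over two treatment-versus-placebo comparisons, "Dunnett procedure will be applied to the ANCOVA-adjusted (least squares) means". It also fixes the analysis set: "Observed values from the per-protocol population will be used for the primary analysis". Compliance means three primary videos or units. Under Postintervention Follow-Up, anyone with no assessment within 2 weeks of the scheduled date counts as lost for that time point.

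Strengths and Limitations lists a "large sample (n=1000) providing adequate power for primary comparisons".

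**The concern.** Two things do not line up.

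- **The test.** The sizing text works at a critical alpha of .05 and does not mention the two comparisons. The analysis text uses a stricter per-comparison threshold.
- **The analysis set.** The 100 recruits above 3 × 300 are assigned to attrition alone. The primary analysis loses participants in two ways: no follow-up assessment, and too little app use. Compensation depends on questionnaires, not app use (End of Trial), so it does not directly support compliance.

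This is a registered report, and recruitment has not begun. Its stated power will shape how a null result for either app is read. If true power is nearer 70% than 80%, a null would carry less weight than the text implies.

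**Working it through.** **Inputs from the protocol.** d = 0.3; power 80%; critical alpha .05; correlation 0.7; 1:1:1 allocation; 300 per arm; 1000 in total; Dunnett over two comparisons. Sidedness is not stated.

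**1. The single-outcome figure.** Normal approximation, two-sided .05: n = 2 × ((1.960 + 0.842)/0.3)² = 174.4. The t-based solution is 175.4, which rounds up to 176, as stated. A one-sided test would give 138. So 176 is an unadjusted two-sided calculation.

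**2. The Dunnett threshold.** Two comparisons share one placebo arm of equal size, so the test statistics correlate at 0.5. Solving P(|Z₁| ≤ c and |Z₂| ≤ c) = 0.95 gives c = 2.212, or .027 per comparison. The single-outcome n becomes 2 × ((2.212 + 0.842)/0.3)² = 207.2, so 208. The ratio 207.2/174.4 is 1.19.

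**3. The allowance for loss.** 3 × 300 = 900, and 1 − 900/1000 = 10%, covering non-response and non-compliance together.

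**4. The simulation figure.** The 300 cannot be reproduced, because the subset proportions and the simulated test are not shown. It can only be calibrated. I take both end points as required (inferred) and a share p of each arm qualifying for each end point. Then

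m = d × √(n·p/2), and power = Φ₂(m − c, m − c; r).

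Fitting p to give 80% at n = 300 and c = 1.960:

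- Model A, r = 0.7: p = 0.697 (209 per end point), m = 0.3 × √(209.2/2) = 3.07.
- Model B, everyone in at least one subset, so overlap is 2p − 1 and r = 0.7(2p − 1)/p: p = 0.731, r = 0.44, m = 0.3 × √(219.3/2) = 3.14.

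Model B fits the eligibility rule better. A is kept to show how little the choice matters.

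**5. Change only c to 2.212.** Power per app; losses above 10% are assumptions:

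| Analysable per arm | Total loss from 1000 | Power at c = 1.960 | Power at c = 2.212 |
|---|---|---|---|
| 333 | 0% | 85% | 77% |
| 300 | 10% | 80% | 71–72% |
| 267 | 20% | 74–75% | 64–65% |
| 233 | 30% | 67–68% | 56–58% |
| 200 | 40% | 58–60% | 47–49% |

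With Dunnett, 80% needs about 350 analysable per arm, or 3 × 350 = 1050, more than the 1000 to be recruited.

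**6. Other decision rules.** Calibrating the 300 to a single end point gives 72–73% at 300 and 77% at 333. Calibrating to at least one end point gives 70% and 75%.

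**7. The covariate.** If d = 0.3 is on the unadjusted scale and the simulation omitted the baseline score, ANCOVA with baseline-to-post correlation ρ raises the effective d to 0.3/√(1 − ρ²). With Dunnett:

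- ρ = 0.4: d = 0.327, power about 81% at 300 per arm.
- ρ = 0.5: d = 0.346, power about 81% at 267 per arm.

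The values of ρ are assumptions; the protocol gives none.

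**The case against.** The strongest reply is that the simulation is not shown. Its critical alpha of .05 could be a familywise level with Dunnett already applied, and the unadjusted reading of 176 belongs to a separate sentence about regular power analyses. That possibility stands, though the text does not state it, and the list of factors reflected leaves out the two comparisons.

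Second, the protocol itself says that adjusting for baseline improves precision. If the simulation left the covariate out, a moderate correlation recovers what Dunnett costs. This also stands. Neither 71–72% nor 81% at 300 per arm is established.

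Third, the rule that both end points must succeed is inferred. The protocol says that coprimary end points reduce power, which favours that reading, but no passage sets the rule. Recalibrating to the other rules leaves a similar shortfall, so this affects how the rerun is specified more than the conclusion.

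Fourth, no document supports losses of 20–40%. The three-unit threshold is low, there are daily reminders, and payment is tied to questionnaires. A condensed article may also leave its attrition rationale to a fuller document. So those rows show sensitivity and are not a forecast. The 10% ceiling, however, is arithmetic from stated figures. Loss through non-compliance would not arise under the intention-to-treat analysis with imputation, but that is listed as a sensitivity analysis.

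**Conclusion.** The 80% figure is not supported for the primary test and analysis set as written. If the simulation used unadjusted .05 and d = 0.3 already reflects the covariate, power per app is about 71–72% at 300 analysable per arm and 77% with no loss at all, and about 350 per arm are needed. Power to succeed for both apps together would be lower. The 10% total allowance holds whatever the simulation did.

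A reader might go further and infer that 80% power is disproved, or that the trial is underpowered. The document does not support that. The simulation's test, its use of the covariate and its subset proportions are not shown, and a baseline-to-post correlation of about 0.4 would restore 80% at 10% loss. The point concerns an unsupported statement of power. It does not show a type I error problem or bias in the effect estimates.

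**What to change.** Rerun the existing simulation with the planned primary test (ANCOVA, the Dunnett critical value, and the coprimary decision rule as the sponsor defines it) in the primary analysis set. State in the sample size section whether the original 300 per arm already included Dunnett and the baseline covariate.

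In Sample Size Calculation and in Strengths and Limitations, report power at N = 1000 for a range of total loss, for example 10%, 20%, 30% and 40%, counting non-response and non-compliance together. Give the smallest effect detectable at 80% power for each. Keep the description as 80% or adequate power only if the rerun shows it.

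The cost is a rerun of existing code and possibly a less favourable stated figure. No extra participants are needed, and the restatement itself leaves the test and the analysis set unchanged.
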